#### Recruitment procedure

2.2.3

Potential participants will be identified during attendance for relevant reproductive or perinatal healthcare services. Recruitment will follow a consecutive invitation strategy, whereby all individuals meeting eligibility criteria during predefined recruitment days and/or shifts will be systematically invited to participate. The initial approach will be made by a healthcare professional not directly involved in the participant’s treatment or assessment. This procedure is intended to minimize selection bias and reduce the possibility of perceived pressure to participate.

At the time of invitation, potential participants will be informed about the purpose of the study, the nature of the questionnaire, the estimated duration of participation, the voluntary nature of participation, and the absence of any consequences for medical care in the event of refusal or withdrawal. Participants who agree to take part will be provided with the participant information sheet and asked to complete informed consent before accessing the questionnaire.

Partner recruitment will occur only after the woman has been informed that partner participation is optional and has had an opportunity to consider this separately from her own enrollment. Women will be able to decline partner involvement without giving a reason, and this decision will not be disclosed to partners, accompanying persons, or clinical staff involved in their care. Where partner recruitment is considered appropriate, partners will receive separate study information, provide independent informed consent, and complete the questionnaire separately. Partner invitation will not be pursued if privacy cannot be ensured or if there is any indication that partner involvement could increase risk, pressure, or discomfort for the woman, including concerns related to intimate partner violence, reproductive coercion, family separation, or conflict-related stress.

To promote consistent recruitment, no targeted selection will be undertaken based on psychological condition, trauma history, or other non-eligibility characteristics; instead, all potentially eligible individuals will be approached according to the same predefined procedure. The participant’s journey is summarized in **Figure 1**.

**Figure 1 f1:**
[figure not shown]
Participant’s journey flowchart.

### Data collection

2.3

Data will be collected using web-based questionnaires administered via the 1KA (RRID: SCR_019283) survey platform. Participants will access the survey through a QR code or direct hyperlink and may complete it either on site at the recruiting healthcare facility or remotely. The study will use two digital data collection instruments. The first will be a participant-completed questionnaire administered to eligible women and, where applicable, to partners included in the supplementary dyadic component. Question flow will be adapted through programmed routing logic so that participants are presented only with items relevant to their reproductive stage and experiences. The second instrument will be completed by authorized healthcare personnel only where participants have provided specific consent for such data collection. This instrument will be used to record relevant clinical information derived from routine care, including findings from medical observation, functional assessment, and laboratory or instrumental examinations, where available within the clinical setting. No biological specimens will be collected, processed, or stored specifically for the purposes of this study.

Following completion of the baseline survey, participants will be invited to provide contact details for the purpose of re-contact and follow-up participation. Follow-up invitations will be scheduled relative to each participant’s baseline completion date. The target assessment points will be 3, 6, and 12 months after baseline, with acceptable completion windows defined as 2.5–3.5 months for the 3-month assessment, 5–7 months for the 6-month assessment, and 10–14 months for the 12-month assessment. The exact date of questionnaire completion and the number of days since baseline will be recorded for each wave. Assessments completed outside these windows will be flagged during data management and considered in sensitivity analyses where relevant. In longitudinal models, time will be represented primarily by assessment wave, with elapsed time since baseline examined where deviations from the target schedule are substantial. Participants who agree to follow-up contact will receive invitations by email at each follow-up wave. Contact details collected for this purpose will be stored separately from questionnaire responses and will not be incorporated into the analytical dataset. Participants will retain the right to decline participation at any follow-up wave without consequence. The total duration of data collection is expected to range from approximately 3 to 12 months, depending on recruitment rates and follow-up completion.

To support study administration and data quality monitoring, the survey platform will record limited process metadata, including date of survey completion, response status, and item-level missingness. These metadata will be used solely for monitoring completeness, identifying duplicate or invalid entries where applicable, and supporting data quality review. At the end of the questionnaire, participants will be provided with information on relevant mental health and lactation support resources, together with contact details for the research team.

To enable confidential linkage of dyadic data while minimizing identifiability, participant records within couples will be matched using a self-generated identification code (SGIC). Each member of the couple will complete the survey independently. The identification code will be constructed according to the procedure described by Harani and Ben-Porat (88), whereby each couple generates a ten-character code composed of the first initials of both partners and their respective two-digit birth months and days (e.g., NS04231017). The first respondent will share the code with the partner to facilitate accurate matching, and a designated questionnaire item will distinguish respondents within the dyad. Because generating or sharing a dyadic code may create privacy or safety concerns in some relationships, participants will be instructed to proceed with partner linkage only if this can be done safely and voluntarily. If sharing the code would be uncomfortable, unsafe, or impractical because of conflict-related separation, relationship strain, domestic violence, reproductive coercion, or lack of privacy, the participant may complete the questionnaire without partner linkage. Cases that cannot be matched at the dyadic level will be retained for individual-level analyses where otherwise eligible but will be excluded from analyses requiring paired data. This approach safeguards participant anonymity while facilitating dyadic analysis and aligns with the Sex and Gender Equity in Research (SAGER) guidelines (89).

All data will be collected in anonymized form, with only indirect identifiers retained for dyadic matching. Any contact information collected for follow-up purposes will be stored separately from survey responses and will be accessible only to authorized members of the research team. Variables used for dyadic linkage or follow-up administration will be retained only for as long as necessary to complete matching and longitudinal follow-up procedures and will subsequently be deleted from the working dataset and stored separately under restricted access, in accordance with the study Data Management Plan (87).

### Measures

2.4

The study will employ a combination of self-report questionnaires and clinician-recorded indicators to assess the variables of interest. The characteristics of the selected measures are presented in **Table 1**, whereas the available evidence regarding the validity and reliability of the measures is summarized in **Table 2**. The assessment schedule, including variations by cohort and wave of data collection, is presented in **Table 3**. Where no validated Ukrainian-language version of a measure was available, translation was undertaken during protocol development by members of the study team, [name], [name], and [name], in accordance with Brislin’s framework (90) and Cruchinho et al.’s recommendations (91). Before the launch of the main cohort study, translated and adapted measures will undergo a preliminary pilot-testing phase to assess item clarity, cultural and contextual appropriateness, acceptability, survey routing, completion burden, and technical functioning of the web-based questionnaire. Feedback from this phase will be used to make minor wording or procedural refinements before the instruments are used in the longitudinal cohort. This pilot phase is intended to support feasibility and content clarity rather than to replace formal psychometric validation. The psychometric evaluation of these Ukrainian-language versions is planned as part of the main study, where adequate sample size is available, and will be reported separately.

**Table 1 T1:** Characteristics of the included measures.

Measure	Source		Items	Response format	Number of Factors	Factor structure	Score range	Cut-off value
	Original measure	Ukrainian version						
ACT-PNM	Rodríguez-Muñoz et al. (2023) (86)	Rodríguez-Muñoz et al. (2023) (86)	40	Mixed	N/A	N/A	N/A	N/A
WHO-5	World Health Organization (1998) (100)	Lotzin et al. (2023) (73)	5	Likert scale (0–5)	1	Unidimensional	0–25 (0–100)*	50*
EPDS	Cox et al. (1987) (104)	Chrzan-Dętkoś et al. (2026) (111)	10	Likert scale (0–3)	3	Anhedonia; anxiety; depression	0–30	13
City BiTS	Ayers et al. (2018) (108)	Chrzan-Dętkoś et al. (2026) (111)	29	Likert scale (0–3)	2/4	2-factor: Birth-related symptoms; general symptoms. 4-factor: Re-experiencing; avoidance; negative cognitions and mood; hyperarousal	0–60	29
City BiTS (Partner Version)	Webb et al. (2021) (126)	—	29	Likert scale (0–3)	2/4	2-factor: Birth-related symptoms; general symptoms. 4-factor: Re-experiencing; avoidance; negative cognitions and mood; hyperarousal	0–60	—
BSS-R	Martin & Martin (2014) (130)	—	10	Likert scale (0–4)	3	Quality of care provision; women’s personal attributes; stress experienced during labor	0–40	—
DAP	Rocca et al. (2019) (118)	—	14	Likert scale (0–4)	3	Cognitive desires and preferences; affective feelings and attitudes; anticipated practical consequences	0–4	—
LMUP	Barrett et al. (2004) (121)	—	6	0–2	1	Unidimensional	0–12	—
MSP/PSP	Jawed-Wessel et al. (2016) (135)	—	MSP: 6 PSP: 8	Likert scale (1–6)	1	Unidimensional	1–6	—
MASQ	Patrick et al. (2011) (138)	—	9	Likert scale (1–5)	3	Values; health; not ready	1–5	—
DVMAS	Peters (2008) (139)	—	18	Likert scale (1–7)	4	Minimization; exoneration; behavior blame; character blame	1–7	—
GAD-7	Spitzer et al. (2006) (112)	Aleksina et al. (2024) (115)	7	Likert scale (0–3)	1	Unidimensional	0–21	7
IES-R	Weiss & Marmar (1997) (92)	Krupelnytska et al. (2025) (97)	22	Likert scale (1–5)	3	intrusion; avoidance; hyperarousal	22–110	30
SCI-2-SF	De Luca et al. (2024) (116)	Yatsenko et al. (2024) (117)	9	Likert scale (0–4)	5	Entrapment; affective disturbance; loss of cognitive control; hyperarousal; social withdrawal	0–4	—
ACE	Felitti et al. (1998)	Lotzin et al. (2023) (73)	10	Dichotomous	N/A	N/A	0–10	N/A

*, raw WHO-5 multiplied by 4 to obtain standardized score ranging from 0 to 100; the cut-off value of 50 refers to the transformed 0–100 score.

**Table 2 T2:** Psychometric evidence for the study measures.

Measure	Version	Validation source	Internal consistency	Test–retest/procedural reliability	Item-level evidence	Factor structure/model fit	Validity/diagnostic accuracy
WHO-5	Original	World Health Organization (1998) (100)	α = .84	Not reported	Not reported	Loevinger’s H = .56	Not reported
EPDS	Original	Cox et al. (1987) (104)	α = .87; split-half reliability = .88	Not reported	Not reported	Not reported	Sensitivity = .86; specificity = .78; PPV = .73
	Ukrainian	Chrzan-Dętkoś et al. (2026) (111)	α = .86–.87; subscale α = .73–.85	Not reported	Item-total r = .35–.73	CFA: χ²(32) = 55.34–79.29, CFI = .97, TLI = .96, RMSEA = .06, SRMR = .04	Convergent validity: r = .44–.72
City BiTS	Original	Ayers et al. (2018) (108)	α = .92; subscale α = .83–.88	Not reported	Not reported	KMO = .94; Bartlett’s χ²(190) = 10,283.1, p <.001; EFA supported a two-factor structure, explaining 56.3% of variance	Convergent validity: r = .50–.61
	Ukrainian	Chrzan-Dętkoś et al. (2026) (111)	α = .92; ω = .92; subscale α = .73–.91; subscale ω = .80–.92	Not reported	Item-total r = .27–.76	CFA: CFI = .949, TLI = .932, RMSEA = .062, AIC = 450.29; ECV = .544, ωH = .635, H = .916	Convergent validity: r = .36–.53; divergent validity: r = .31–.61
City BiTS (Partner version)	Original	Webb et al. (2021) (126)	α = .94; subscale α = .78–.92	Not reported	Not reported	KMO = .926; Bartlett’s χ²(190) = 3745.14, p <.001; EFA supported a two-factor structure, explaining 50.81% of variance	Not reported
BSS-R	Original	Martin & Martin (2014) (130)	α = .79; subscale α = .64–.74	Not reported	Not reported	CFA: χ²(32) = 42.67, p = .10, χ²/df = 1.33, CFI = .98, RMSEA = .04, RMR = .04, SRMR = .05	Not reported
DAP	Original	Rocca et al. (2019) (118)	α = .95–.96; separation reliability = .90–.91	ICC = .95	Item-total r = .53–.83	Not reported	Sensitivity = .78; specificity = .81
LMUP	Original	Barrett et al. (2004) (121)	α = .92	Test–retest κ = .97; long-term κ = .86	Item-total r = .60–.89	PCA supported a one-factor structure; eigenvalue = 4.33; loadings = .70–.93	Not reported
MSP/PSP	Original	Jawed-Wessel et al. (2016) (135)	MSP: α = .89; PSP: α = .91	Not reported	Factor loadings: MSP = .74–.85; PSP = .77–.92	EFA supported a one-factor structure for MSP, explaining 64.58% of variance, and a one-factor structure for PSP, explaining 69.35% of variance	Not reported
MASQ	Original	Patrick et al. (2011) (138)	α = .75–.94	Not reported	Not reported	EFA supported a six-factor structure, explaining 66.83% of variance; CFA: CFI = .93–.94, RMSEA = .03–.05	Not reported
DVMAS	Original	Peters (2008) (139)	α = .88	Not reported	Not reported	Four-factor structure reported	Correlations with related constructs: RMA r = .65, SRS r = .51, ATW r = .47, AWA r = .37
GAD-7	Original	Spitzer et al. (2006) (112)	α = .92	Retest ICC = .83; procedural ICC = .83	Not reported	Not reported	Sensitivity = .89; specificity = .82
	Ukrainian	Aleksina et al. (2024) (115)	α = .88–.90; ω = .87–.89; λ6 = .88–.90; split-half reliability = .83–.87	Retest r = .72	Item-total r = .73–.85	EFA supported a one-factor structure, explaining 52.3%–57.1% of variance; CFA: CFI = .973–.985, TLI = .959–.977, RMSEA = .064–.078	Not reported
IES-R	Original	Weiss & Marmar (1997) (92)	α = .79–.92	Retest r = .51–.94	Not reported	EFA supported a three-factor structure	Not reported
	Ukrainian	Krupelnytska et al. (2025) (97)	α = .91; ω = .92; subscale α/ω = .75–.84	Retest ICC = .206; retest r = .412	Not reported	CFA: CMIN/DF = 2.874, RMSEA = .049, SRMR = .065, CFI = .977, TLI = .974	Not reported
SCI-2-SF	Original	De Luca et al. (2024) (116)	Not reported	Not reported	Not reported	Not reported	AUROC = .824–.856
	Ukrainian	Yatsenko et al. (2024) (117)	α = .88; ωH = .84; subscale α = .43–.79	Not reported	Factor loadings >.40	CFA: RMSEA = .033, CFI = .98, TLI = .98, SRMR = .05; MSA = .91	Convergent validity: r = .210–.421; divergent validity: r = −.358

α, Cronbach’s alpha; ω, McDonald’s omega; ωH, hierarchical omega; λ6, Guttman’s lambda 6; ICC, intraclass correlation coefficient; κ, kappa coefficient; PPV, positive predictive value; EFA, exploratory factor analysis; CFA, confirmatory factor analysis; PCA, principal component analysis; KMO, Kaiser–Meyer–Olkin measure; CFI, comparative fit index; TLI, Tucker–Lewis index; RMSEA, root mean square error of approximation; SRMR, standardized root mean square residual; RMR, root mean square residual; AIC, Akaike information criterion; ECV, explained common variance; H, construct replicability index; MSA, measure of sampling adequacy; AUROC, area under the receiver operating characteristic curve; RMA, rape myth acceptance; SRS, sex-role stereotyping; ATW, attitudes toward women; AWA, adversarial sexual beliefs.

**Table 3 T3:** Schedule of measure administration across study assessment waves.

Measure	Cohort															
	Non-pregnant women				Pregnant women				Postpartum women				Partners			
	T1	T2	T3	T4	T1	T2	T3	T4	T1	T2	T3	T4	T1	T2	T3	T4
Participant-completed measures																
ACT-PNM	+	+	+	+	+	+	+	+	+	+	+	+	+	+	+	+
WHO-5	+	+	+	+	+	+	+	+	+	+	+	+	+	+	+	+
EPDS					+	+	+	+	+	+	+	+				
City BiTS									+	+	+	+				
City BiTS (Partner version)													+	+	+	+
BSS-R									+	+	+	+				
DAP	+	+	+	+												
LMUP					+	+		+	+	+		+				
MSP/PSP					+	+	+	+					+	+	+	+
MASQ	+			+	+	+	+	+	+	+	+	+	+	+	+	+
DVMAS	+			+	+			+	+			+	+			+
GAD-7	+	+	+	+	+	+	+	+	+	+	+	+	+	+	+	+
IES-R	+	+	+	+	+	+	+	+	+	+	+	+	+	+	+	+
SCI-2-SF	+	+	+	+	+	+	+	+	+	+	+	+	+	+	+	+
ACE	+				+				+				+			
Clinician-recorded measures																
Laboratory assessment	+	+	+	+	+	+	+	+	+	+	+	+				
Imaging assessment	+				+				+							
Obstetric parameters					+	+	+	+								
Fetal assessment					+	+	+	+								
Perinatal parameters									+							
Neonatal screening									+							

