#### Sample size

2.2.1

The sample size was estimated for the primary longitudinal mixed-model repeated-measures analysis, with the World Health Organization–Five Well-Being Index (WHO-5) score anchored as the primary outcome. Accordingly, the calculation was designed to provide adequate statistical power to detect differences in longitudinal WHO-5 trajectories according to war-related stress exposure. Sample size estimation was conducted in R (RRID: SCR_001905) using the *longpower* package (80). Parameter values were derived from previously published longitudinal studies, consistent with Harrall et al.’s recommendations (81). Given the substantial logistical and participant burden associated with data collection during an ongoing war, statistical power was set at 0.8, and the type I error rate was set at 0.05. Equal allocation across the two comparison levels specified in the power model was assumed.

The standard deviation of the WHO-5 outcome among postpartum women was set at 1.05, based on data reported by Mor et al. (82). The correlation structure was specified as a first-order autoregressive process with a correlation parameter of 0.38, informed by longitudinal data reported by Qandil et al. (83). Retention assumptions were based primarily on the cumulative follow-up pattern reported by Damtew et al. (84), with retention rates of 92.9% at 6 weeks, 84.2% at 6 months, and 73.0% at 12 months, calculated using the baseline cohort as the denominator at each follow-up. Although some studies in post-conflict settings have reported relatively high retention, such as the 77.3% 2-year retention reported by Silove et al. (85), the present assumptions were considered more appropriate for this study context.

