##### London measure of unplanned pregnancy

2.4.3.2

The London Measure of Unplanned Pregnancy (LMUP) is a self-report instrument developed to assess the degree to which a pregnancy was planned (121). The instrument comprises six items, each scored from 0 to 2, yielding a total score ranging from 0 to 12, with higher scores indicating greater pregnancy planning. The original validation study demonstrated strong psychometric properties, including high internal consistency, test–retest reliability, and construct validity (121). The measure has also been validated in several languages and contexts, including Italian (122), Krio (123), and Turkish (124), and has been shown to be informative when integrated into routine antenatal care (125). In the present study, the Ukrainian translation of the measure was prepared by the authors, and its psychometric properties will be evaluated within the current sample.

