### Data analysis

2.5

Analyses will be conducted in R (RRID: SCR_001905) using longitudinal modeling approaches. The primary analytic aim is to estimate trajectories in prespecified primary mental health outcomes and to test whether trajectories differ by war-related stress exposure. The main exposure will be cumulative war-related stress exposure, derived from predefined ACT-PNM domains, including displacement, family separation, disruption of healthcare access, economic hardship, and direct or indirect exposure to threat. In primary mixed-effects models, war-related stressor exposure will be represented by baseline ACT-PNM-derived stressor burden, and the main test of the study hypothesis will be the interaction between stressor burden and time in predicting trajectories of the primary mental-health outcome family. The primary trajectory contrast will be the war-related stress exposure-by-time interaction across baseline, 3-month, 6-month, and 12-month assessments, with baseline-to-12-month change treated as the principal longitudinal contrast. Secondary aims will examine reproductive intentions, pregnancy planning, reproductive-status transitions, and cohort-specific perinatal outcomes. Exploratory analyses will examine dyadic partner data, sexual attitudes, domestic-violence myth acceptance, and clinician-recorded obstetric, maternal, fetal, and neonatal indicators.

Before analysis, the dataset will be checked for completeness, duplicate submissions, invalid response categories, incompatible units, out-of-range values, inconsistent reproductive status, and temporal inconsistencies between key clinical events. Examples of such inconsistencies include delivery dates preceding pregnancy-related assessments, postpartum status recorded before childbirth, gestational age values outside plausible ranges, or incompatible pregnancy outcome categories. Values will not be reconstructed from other variables unless the derivation rule has been specified in advance.

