Baseline reproductive status will be included to account for cohort-entry differences between non-pregnant, pregnant, and postpartum participants. In addition, reproductive status assessed at each wave will be modeled as a time-varying covariate when participants transition between reproductive states during follow-up. Where sample size permits, interactions between time, war-related stress exposure, and reproductive status will be examined to assess whether mental-health trajectories differ across reproductive stages. Primary longitudinal analyses will be conducted in the women’s cohort. Mixed-effects growth models will include repeated observations nested within participants and will estimate mental-health trajectories across the four assessment waves. Baseline reproductive status will be included as a cohort-entry characteristic to account for initial differences between non-pregnant, pregnant, and postpartum participants.

Reproductive transitions will also be examined as secondary longitudinal outcomes. Combining groups in this framework is justified because mixed-effects models allow unequal numbers of observations, time-varying covariates, and adjustment for baseline reproductive status. Transition variables will be derived between waves, including, where applicable, becoming pregnant, giving birth, having pregnancy or neonatal loss, entering the postpartum period, remaining in the same reproductive-status group, or other documented reproductive-status changes. Binary transitions will be analyzed using generalized mixed-effects models with a logit link, whereas transitions with more than two categories will be modeled using multinomial or alternative categorical longitudinal models, depending on event frequency and model stability. These analyses will be interpreted as secondary or exploratory if the number of observed transitions is limited.

Values resulting from planned non-administration of a measure (see **Table 3**) will be coded as structurally non-applicable and will be distinguished from missing data due to item nonresponse or loss to follow-up. Structurally non-applicable values will not be imputed or treated as participant-level missingness. Analyses of cohort-specific measures will therefore be restricted to the eligible reproductive-status group or wave, while mixed-effects models will use all available repeated observations for variables applicable across groups.

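### Table 3 omits LMUP at the 6-month wave, so a pregnancy first reported then is scored only at 12 months or never, and the table does not say whether its columns follow baseline or current status

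*Protocol article*

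**What the plan says.** Section 2.4.3.2 describes LMUP as a "self-report instrument developed to assess the degree to which a pregnancy was planned". It has six items, is listed as a secondary outcome measure, and its Ukrainian translation is to be evaluated in this sample. Section 2.5 states: "Secondary aims will examine reproductive intentions, pregnancy planning, reproductive-status transitions, and cohort-specific perinatal outcomes". The same section derives becoming pregnant as a between-wave transition.

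The timing of LMUP is fixed in section 2.4, Table 3 ("Schedule of measure administration across study assessment waves"). Pregnant and postpartum women have T1, T2 and T4. Non-pregnant women and partners have no wave. Section 2.4.3.2 gives no reason for leaving out T3.

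On wave timing, section 2.3 says: "The target assessment points will be 3, 6, and 12 months after baseline", with windows of "2.5–3.5 months for the 3-month assessment, 5–7 months for the 6-month assessment, and 10–14 months for the 12-month assessment". On routing, it says that "participants are presented only with items relevant to their reproductive stage and experiences". Section 2.5 codes planned blanks separately: "Structurally non-applicable values will not be imputed or treated as participant-level missingness".

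**The concern.** An LMUP score belongs to one particular pregnancy. The schedule can score a pregnancy present at baseline three times, yet it does not ask at T3, the wave at which a pregnancy begun roughly between months 3 and 6 first comes to light.

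Pregnancies that start during follow-up in women who enter non-pregnant are the ones for which DAP and baseline war-related exposure are recorded before conception. They are the pregnancies in which earlier intention and exposure can be related to later planning, and section 2.2 gives the chance of observing changes in pregnancy-planning intentions as one reason for enrolling non-pregnant women. A late or absent LMUP weakens that part of the secondary aim. The table also leaves open whether a woman who changes status moves to another column, and on one reading these pregnancies are not scored at all.

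**Working it through.** **1. The LMUP row, cell by cell (four cohorts, four waves)**

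- Non-pregnant: none
- Pregnant: T1, T2, T4
- Postpartum: T1, T2, T4
- Partners: none

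The T3 gap is the same in both cohorts that receive LMUP, and other rows (DVMAS, ACE) also use blanks for planned non-administration. An extraction fault is therefore unlikely.

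**2. What happens to a woman who enters non-pregnant and first reports a pregnancy at T3**

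- Columns follow current status (suggested by the stage-based routing in section 2.3): at T3 she is in the pregnant column, which is blank. At T4 she is in the pregnant or postpartum column and is scored. If the pregnancy was lost and she is non-pregnant again, she is in a column with no LMUP.
- Columns follow baseline cohort (section 2.2.2 defines the three groups as baseline cohorts): she stays in the non-pregnant column and never receives LMUP, whenever she conceives.

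**3. Gestation at T4 under the current-status reading**

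Inputs from section 2.3: T2 = 3, T3 = 6, T4 = 12 months. Assumptions not in the document: conception is reportable r = 0.25 to 1.0 month later, conceptions are evenly spread between waves, 1 month = 365.25/12/7 = 4.348 weeks, and gestational age = weeks since conception + 2.

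A pregnancy first reported at T3 was conceived between T2 − r and T3 − r.

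- Least advanced at T4: (12 − (6 − 0.25)) × 4.348 + 2 = 29.2 weeks
- Most advanced at T4: (12 − (3 − 1.0)) × 4.348 + 2 = 45.5 weeks, that is, after birth
- Spread over r: 35–60% at 28–36 weeks, 23% at 37–39 weeks, 17–42% at 40 weeks or more
- If asked at T3 instead: from 0.25 × 4.348 + 2 = 3.1 to (6 − 2) × 4.348 + 2 = 19.4 weeks

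Window extremes: with T3 at 7 and T4 at 10 months, the earliest is (10 − 6.75) × 4.348 + 2 = 16.1 weeks. With T2 at 2.5, T3 at 5 and T4 at 14 months, the earliest is (14 − 4.75) × 4.348 + 2 = 42.2 weeks, so all fall after term. With timing uniform inside the windows and r = 0.5, about 10% are below 28 weeks, 41% at 28–36, 16% at 37–39 and 33% at 40 or more.

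**4. Dropout between T3 and T4**

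Section 2.2.1 gives main retention of "92.9% at 6 weeks, 84.2% at 6 months, and 73.0% at 12 months" and conservative proportions of 0.72 at T3 and 0.52 at T4. The conservative figures reproduce: 0.85² = 0.7225 and 0.85⁴ = 0.522.

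- Main: 1 − 73.0/84.2 = 13.3%
- Conservative: 1 − 0.52/0.72 = 27.8%

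**5. Share of all pregnancies starting in follow-up**

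If conceptions are evenly spread over 12 months (assumption), months 3–6 hold 3/12 = 25%. Loss of LMUP through T3–T4 dropout is then 0.25 × 13.3% = 3.3%, or 0.25 × 27.8% = 7.0%, before any pregnancy losses. The document gives no expected number of new pregnancies, so this cannot be turned into a count of women.

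**The case against.** The case for leaving the schedule alone has real force.

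- **Recall.** A reader might infer that a six-month delay biases the score because the outcome of the pregnancy may be known by then. The document does not support that. Postpartum women already answer LMUP at entry up to 12 months after birth, and Table 2 cites a long-term kappa of .86. That figure is for the original instrument, but nothing in the protocol shows harm from the delay itself.
- **Timing.** A reader might infer that T4 always falls around term. It does not: on the target schedule roughly a third to three fifths of these women would be at 28–36 weeks, and the windows allow mid-pregnancy.
- **Hidden loss.** A reader might infer that the rule on planned blanks conceals the dropouts. It does not. Under the current-status reading a missed T4 is loss to follow-up and is counted as such; only the T3 cell is non-applicable.
- **Selective loss.** The retention figures are for the whole cohort and do not show that women with a new pregnancy leave differently.
- **Other information.** DAP is given to non-pregnant women at every wave, and section 2.2.2 updates pregnancy intention during follow-up. Intention before conception is therefore recorded, although neither is an LMUP score.
- **Status of the outcome.** Section 2.2.1 calls the secondary analyses hypothesis-generating.

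These points limit the size of the problem. They do not explain the T3 blank, recover the score after a dropout or pregnancy loss, or settle what the columns mean.

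**Conclusion.** The point stands as a low-cost improvement to a secondary outcome. It has no bearing on the primary WHO-5 analysis or the sample size. Under the current-status reading, pregnancies first reported at 6 months are scored at about 29–45 weeks or after birth on the target schedule, against about 3–19 weeks if asked at T3. Of these, 13.3% (main) to 27.8% (conservative) would go unscored through dropout, plus those ending in a loss after which the woman is again non-pregnant. Under the baseline-cohort reading, no pregnancy in a woman who enters non-pregnant is scored. The article does not say which reading applies, and both leave a gap.

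The gestational ages rest on the assumed reporting delay and even spread of conceptions. The dropout figures rest on the plan's own retention assumptions applying to these women. Women already pregnant or postpartum at T1, or first reporting a pregnancy at T2 under current-status routing, are covered.

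**What to change.** Add a routing rule to Table 3: LMUP is given at the first wave, T1 to T4 and including T3, at which a new current or completed pregnancy is reported, including one that ended in loss, whatever the woman's baseline cohort. Index each score to the pregnancy it describes, so that scores for different pregnancies in one woman are kept apart. State beside the table whether its columns follow baseline cohort or current status.

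The existing repeat administrations can stay, since they serve the planned psychometric evaluation of the new translation.

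The cost is one table row, one routing condition, and six extra items at one wave for women with a new pregnancy. For women reporting a loss, the items would need to follow the bereavement-sensitive wording and routing already planned in section 2.6.1.
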